**1. INTRODUCTION**

1.1 Scientific background

In malignant bile duct stenosis, a small percentage of patients with malignant bile duct stenosis fail to undergo endoscopic retrograde cholangiopancreaticography (ERCP). This is due to anatomical changes or a non-cannulated papilla. Percutaneous Transhepatic Cholangiodrainage (PTBD) has been the method of choice for years after unsuccessful ERCP and is widely available. However, numerous publications have reported a relatively high complication rate and 30-day mortality of up to 33% (1), making it necessary to establish a new reserve procedure for bile duct drainage. With endosonographically guided cholangiodrainage (EUCD), such a procedure has been established in recent years, since the initial description by Giovannini M in 2001 (2). In EUCD, the bile duct is punctured transmurally (through the stomach or intestinal wall) from inside the body. Four main drainage procedures are used: EUS-guided antegrade drainage via the papilla (EUS-AD), which is most similar to PTBD in principle, since it maintains the normal anatomy (bile flow via the papilla or jejunal loop in biliodigestive anastomosis), the most common EUS-guided hepaticogastrostomy (EUS-HGS), the EUS-guided choledochoduodenostomy (EUS-CDS) and the EUS-guided rendez vous procedure with ERCP (EUS-RV).

A recently published meta-analysis on percutaneous versus endosonographic bile duct drainage (3) concluded that the technical success rate of both procedures is equivalent, but that PTBD has a lower clinical success rate as well as more complications and a higher rate of re-interventions. It was therefore concluded that endosonographic bile duct drainage should be preferred to PTBD. However, the listed retrospective and prospective comparative studies either provide no information about the PTBD technique performed or use PTBD in the comparative arm in a way that does not correspond to the possibilities of this method.

The following is a commented overview of the comparative studies between PTBD and EUCD (12) (**Table 1**):

| **Author** | **Study type** | **PTBDs (n)** | **Adverse events (n)** | **Re-interventions (mean frequency)** | **Method of PTBD access** | **Special comments** |
| --- | --- | --- | --- | --- | --- | --- |
| Artifon 2012 (4) | Prospective | 12 | 3 (25%) | Not analyzed | fluoroscopic and ultrasound guidance | 4 external drainages before metal stent insertion |
| Bapaye 2013 (5) | Retrospective | 26 | 12 (46 %) | Not analyzed | fluoroscopic guidance | only 12/26 (46%) metal stents and 14/26 (54%) external drainages |
| Kashab 2015 (6) | Retrospective | 51 | 20 (39%) | 0,80 (n=41) | no detailed description | Not reported whether metal stents were used or not, many scheduled re- interventions, many bile leaks (n =17) |
| Sharaiha 2016 (7) | Retrospective | 13 | 7 (54%) | 1.70 (n=22) | no detailed description | benign and malignant bile duct obstruction were mixed, number of metal stents remains unclear |
| Lee 2016 (8) | Prospective | 32 | 10 (31%) | 0,93 (n=29) | fluoroscopic guidance | 2 step intervention: external drainage before metal stent insertion, just 15 (48%) of metal stents inserted |
| Sportes 2017 (9) | Retrospective | 20 | 2 (10%) | 1,05 (n=21) | ultrasound guidance | external drain was left after metal stent implantation and removed some days later when stent implantation was clinically successful, scheduled re-interventions were mixed with unscheduled re-interventions |

A comparative study, in which both methods are used and analysed to their best advantage, would require some conceptual changes. On the one hand, PTBD should be used in an optimal way. The following aspects should be considered (10):

1. The primary puncture of the bile duct should not be performed "blind" under radiological fluoroscopy, but under colour contrast Doppler sonographic control, in particular to avoid the puncture of intrahepatic blood vessels (11)

2. The access route of PTBD should preferably be transxyphoidal via the left lobe of the liver, since fewer complications are to be expected here than with the right access route (pain with intercostal position of the drainage, pleural complications) (12).

3. Whenever possible, metal stent-implantation should be performed in the first session and no external or internal/external plastic drainage should remain percutaneous, as this can lead to complications such as an outward or intra-abdominal bile leakage. (10).

4. Endoscopic visual inspection may be helpful in controlling stent release, as it allows precise control of the placement of the distal end of the stent in the duodenal lumen. In biliodigestive anastomosis, endoscopic control is usually not necessary because the stent usually has enough room to unfold and drain bile in the anastomosed loop of the small intestine (10).

5. A portal vein-oriented puncture of a peripheral bile duct is particularly helpful if the intrahepatic bile ducts are hardly congested (13).

The same applies to EUCD. For this, the best method and the best devices (e.g. in the choice of the metal stent) according to the current state of knowledge should be used (14). As already mentioned, various procedures are available here (transluminal stenting, antegrade stenting while retaining the existing bile duct anatomy and the rendezvous procedure with conventional ERCP). In a recent publication by Tyberg and colleagues, an algorithm was proposed to determine how the respective method should be applied depending on the dilatation of the intrahepatic bile ducts (dilated versus non-dilated) and the success of the rendezvous procedure or the success of an antegrade stenting can take place (in the next step then transluminal, e.g. as EUS-HGS or EUS- CDC) (15). Most of the studies conducted so far have only selectively chosen one of the different procedures of EUCD as a comparative method to PTBD, which could have led to a selection bias.

In contrast, the planned study will compare the three main techniques of EUCD, i.e. antegrade drainage, transhepatic drainage and drainage into the D. common bile duct, with PTBD and its optimizations described above. The specifications for the EUCD were coordinated with a recognized expert in the field of EUCD ([name], Gera). The study will be conducted prospectively, multicentre and non-randomized (reason for non-randomization: each centre offers the technique that it masters best).

1.2 Rational

PTBD and EUCD are recognized reserve procedures for patients with malignant biliary stenosis when ERCP was not successful or not feasible for surgical-anatomical reasons. Both procedures have a certain risk of complications. In previous studies, the technical success rate of both procedures was almost identical, whereas PTBD tended to cause a higher rate of complications, a higher number of reinterventions and a longer hospital stay. However, PTBD was presumably not performed under equivalent, optimised procedures (see 1.1.). It is expected that PTBD in this optimised procedure causes fewer complications and fewer re-interventions are necessary than shown in previous studies. In addition, the occurrence of intervention-related pain is analysed in a standardised manner using a visual analogue scale (18).

On the other hand, the EUCD is a dynamically evolving procedure whose technical equipment and therapeutic algorithms are constantly evolving (19). The planned multicentre study should therefore show how both procedures compare under equivalent conditions and according to current standards in selected centres in Germany. In particular, the success rates, but also the complication and reintervention rates are to be determined, so that finally, if necessary, it can be reformulated which of the two methods would be preferable in future as the primary reserve method according to ERCP.

1.3 Risk-benefit assessment

At the respective study centre, patients with malignant bile duct stenosis are prospectively offered the method that is best mastered there. Either PTBD or EUCD. This way, no additional risk beyond the usual intervention-related risk is incurred. With presumably similar technical and clinical success, the study should show to what extent the higher complication rate, higher rate of reintervention and longer hospital stay attributed to PTBD actually apply. On the other hand, the study offers the opportunity to make the EUCD method and its possibilities and risks even better known.

**2. OBJECTIVES AND ENDPOINTS**

Primary objective and primary endpoint

The primary objective of the study is to show that PTBD is not inferior to EUCD in terms of technical success rate. The technical success rate is defined as the successful implantation of a metal stent into the bile duct system (= successful drainage of the contrast medium via the metal stent within one minute after injection).

The primarily technical success of the intervention is decisive for the further procedure following the examination (reintervention necessary ? surgery necessary ?) and is presumably almost identical to the clinical success of the intervention, which can only be verified after 7 days (drop in bilirubin value ≥ 50%). The technical success rate was therefore preferred to the clinical success rate as the primary endpoint.

In PTBD there is only one possibility of metal stenosis insertion across the tumor stenosis in the common bile duct (blunt). In EUCD, the additional option of transluminal stent placement in the context of EUS-HGS or EUS-CDS remains.

The prompt (1 week) implantation of a metal stent after the application of an external drainage in PTBD is also considered a technical success. However, the application of an external drainage is counted as "reinvention".

Secondary objectives and secondary endpoints

In addition to the technical success rate, both interventions will be compared descriptively with regard to other endpoints. All endpoints or points in time refer to the technically successful intervention.

1. Clinical success rate of bile extraction, defined as reduction of the bilirubin value of ≥ 50% 7 days after technically successful intervention in relation to the baseline value before intervention.

2. The occurrence of at least one complication (including death) within 30 days (description + count)

3. Duration of bile duct intervention (PTBD/EUCD) in minutes

- for PTBD: from the application of the local anaesthetic to the application of the skin dressing

- for the EUCD: from the insertion of the endoscope to the removal of the endoscope

4. Post-interventional pain sensation on day 1 and day 7 after intervention (in relation to baseline before intervention): visual analogue scale

5. Length of hospital stay (from the day of the first intervention to the day of discharge) in days

6. Number of re-interventions between the first intervention and the end of the follow-up

(n) after 6 months.

7. Overall survival (overall survival including any cause of death) and disease specific survival (overall survival which only includes the underlying malignant disease that led to bile duct obstruction)

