The evaluation of further secondary endpoints is done in the ITT set. With regard to the complication rate, PTCD is expected to have a lower complication rate than EUCD. No missing values are implanted during the evaluation of secondary endpoints. The evaluation is purely descriptive. Appropriate statistical methods are used according to the underlying distribution. For continuous endpoints, the mean, standard deviation, median, interquartile distance, and minimum and maximum are reported separately and in total for the two groups. For categorical endpoints, absolute and relative frequencies are given, also separately for the two groups and in total. Event times are displayed and evaluated using survival time analysis methods (e.g. Kaplan Meier). Descriptive p-values are given together with 95% confidence intervals. In the EUCD group, descriptive p-values are also divided by method (see 5.1). In addition, unless defined in the secondary endpoints, adverse events are evaluated and compared.

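### One of the two reasons for making technical success primary, its near-identity with clinical success, conflicts with the evidence cited in Section 1.1, and clinical success as defined leaves out technical failures

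*Protocol*

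**What the plan says.** Section 2 states the aim: "The primary objective of the study is to show that PTBD is not inferior to EUCD in terms of technical success rate". Two reasons for the endpoint follow. The first is practical: "The primarily technical success of the intervention is decisive for the further procedure following the examination". The second is that technical success "is presumably almost identical to the clinical success of the intervention, which can only be verified after 7 days", where clinical success means a fall in bilirubin of at least 50%. The inference is then drawn: "The technical success rate was therefore preferred to the clinical success rate as the primary endpoint".

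Section 1.1 summarises the cited meta-analysis as finding that "the technical success rate of both procedures is equivalent, but that PTBD has a lower clinical success rate". It then objects that the component studies either did not describe their PTBD technique or did not use PTBD to its potential.

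Section 1.2 says that technical success was nearly the same in earlier studies. It lists complications, re-interventions and hospital stay as the points against PTBD, and clinical success is not in that list. Section 1.3 presumes that technical and clinical success will both be similar. Section 1.2 also gives the wider aim, that after the trial "it can be reformulated which of the two methods would be preferable in future as the primary reserve method".

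Clinical success is the first secondary endpoint. Section 2 measures it seven days after a technically successful intervention and says that all secondary endpoints refer to that intervention. Section 9.2 places further secondary endpoints in the ITT set with 95% confidence intervals, does not impute missing values (reading the translated verb in that sense), and adds: "The evaluation is purely descriptive". The only other confirmatory test is on the occurrence of at least one complication, reached after non-inferiority is shown.

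**The concern.** If two arms are equal on technical success and unequal on clinical success, the two outcomes cannot nearly coincide in both arms. The near-identity statement in Section 2 therefore conflicts with the finding reported in Section 1.1, and the protocol does not reconcile them. Near-identity is also the only stated reason that ties the primary endpoint to a benefit for the patient.

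Two things follow. The confirmatory non-inferiority claim concerns an outcome on which the protocol already describes the procedures as equivalent, so a reader could take it to cover drainage effect as well. And the endpoint that measures drainage effect, on which PTBD was reported worse, is defined so that patients whose stent placement failed have no value. A difference in failure rates would then not appear in the clinical comparison.

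**Working it through.** **1. The plan's own figure.** Section 9.1 gives 95% technical success in both arms, margin 0.10, one-sided 2.5%, 80% power, Farrington/Manning test. The restricted rates under the null are 0.9703 and 0.8703.

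- Null SD: √(0.9703·0.0297 + 0.8703·0.1297) = 0.376
- Alternative SD: √(2·0.95·0.05) = 0.308
- n per arm = [(1.960·0.376 + 0.842·0.308)/0.10]² ≈ 99.4 (unrounded inputs), so 100
- With 5% drop-out: 100/0.95 = 105.3, so 106

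Both stated figures reproduce. Power at 100 per arm is 80.3% by the approximation and 83.2% exactly. Clinical success does not enter the test. With 95% technical success in both arms, the chance of declaring non-inferiority is therefore about 80–83% whatever the clinical difference.

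**2. The passages side by side.**

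| Place | Technical success | Clinical success |
|---|---|---|
| Section 1.1 (meta-analysis) | equivalent | lower with PTBD |
| Section 1.2 (earlier studies) | almost the same | not mentioned |
| Section 1.3 | presumed similar | presumed similar |
| Section 2 | primary endpoint | presumed nearly the same as technical success |

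For optimised PTBD, Section 1.2 expects fewer complications and re-interventions. It makes no statement about clinical success.

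**3. What the definition hides.** Let t be technical success and r the bilirubin response among technically successful patients. As defined, the comparison is r(EUCD) − r(PTBD). With failures counted in the ITT set it is t·r(EUCD) − t·r(PTBD). The documents give no r, so the values below are assumed, with r equal in both arms.

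| t, EUCD / PTBD | As defined | ITT, r = 90% | ITT, r = 80% |
|---|---|---|---|
| 95% / 95% | 0 | 0 | 0 |
| 95% / 90% | 0 | 0.90·5 = 4.5 points | 0.80·5 = 4.0 points |
| 95% / 85% | 0 | 0.90·10 = 9.0 points | 0.80·10 = 8.0 points |

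At the planned 95%, about 0.05·106 = 5.3 patients per arm would drop out of the comparison.

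**4. What the planned interval could show.** Assume t = 95% in both arms, r = 90% in EUCD, and 106 per arm. The half-width is 1.96·√[p₁(1−p₁)/106 + p₂(1−p₂)/106].

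| r in PTBD | Clinical success, EUCD / PTBD | Difference | Half-width | 95% interval (points) |
|---|---|---|---|---|
| 90% | 85.5% / 85.5% | 0 | 9.5 | −9.5 to 9.5 |
| 85% | 85.5% / 80.75% | 4.75 | 10.1 | −5.3 to 14.8 |
| 80% | 85.5% / 76.0% | 9.5 | 10.5 | −1.0 to 20.0 |

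**5. Would a formal 10-point test on clinical success work?** Exact power of the same test at 100 per arm, with truly equal rates of 90%, 85% and 80% (assumed), is 62%, 50% and 42%. For 80% power about 155, 207 and 255 per arm would be needed.

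**The case against.** The choice of technical success has a defence. Section 2 gives two reasons, and the first, that the immediate result decides what happens next, is not contradicted anywhere. The second is openly worded as a presumption. Section 1.1 discounts the meta-analysis, and its Table 1 shows why: in two studies only 12 of 26 and 15 (48%) of the PTBD patients received metal stents, and others used external drains or two steps. A gap seen under that practice does not refute a presumption about this trial's PTBD. Complications, also in dispute, are tested confirmatorily. ITT analysis and 95% intervals for secondary endpoints are already planned.

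All of this stands, and it rules out some stronger readings. A reader might infer that the primary endpoint has lost its justification; it has not, because the first reason remains. A reader might infer that the preferable method will be declared on technical success alone; Section 1.2 refers to success, complication and re-intervention rates together. A reader might also want the 10-point limit imposed on clinical success. Section 9.1 justifies that limit for technical success only, and step 5 shows that such a gate would fail in about 38–58% of trials with truly equal arms.

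What remains is that discounting the old evidence does not supply new evidence. The protocol does not use the discount to explain the clinical gap and cites nothing for near-identity under optimised PTBD. Section 7.2.2 anchors clinical success to the completed intervention, which might be read to include failures. But Section 2 refers all secondary endpoints to the technically successful intervention, and Section 6.4 starts the seven-day count there. The ITT label does not bring back patients who have no defined value.

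**Conclusion.** The point holds in a limited form. One of the two stated reasons for the primary endpoint conflicts with evidence the protocol itself reports and is otherwise unsupported. Clinical success, the outcome on which PTBD was reported worse, is descriptive and as defined excludes technical failures. The sample size and primary test are not in error.

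The size cannot be derived from the documents. Under the assumptions in step 3, the definition would hide about 4 to 4.5 points for a 5-point difference in technical success, and 8 to 9 points for a 10-point difference. If technical success is equal in both arms and r is also equal, it hides nothing. The example of 85.5% against 76.0% is likewise an assumption. It shows that a positive primary result could coexist with an interval reaching 20 points, not that such a deficit exists.

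**What to change.** Keep the primary endpoint, the test, the margin and the sample size. Change the wording in four places:

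- **Section 2, rationale.** Remove the near-identity statement or mark it as an untested assumption, and let the first reason carry the choice.
- **Sections 2 and 7.2.2, clinical success.** Define it for every patient in the ITT set, with technical failures counted as clinical failures, and use the same definition in both sections.
- **Section 9.2.** Report the EUCD minus PTBD difference in clinical success with the 95% interval already planned, beside the primary result. Do not apply the 10-point technical-success limit to it as a formal gate.
- **Sections 1.2 and 9.2, conclusion.** State that a positive primary test supports non-inferiority in technical success only, and that any statement on the preferable method also weighs the clinical success interval, complications and re-interventions.

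The cost is protocol and SAP text and one redefined denominator, using bilirubin values already collected at baseline and day 7. No patients are added. The downside is slightly lower reported clinical success rates and a narrower headline claim.

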6.3 Treatment rounds (intervention day)

Characterisation of the respective intervention: PTBD or EUCD (Case Report Form, p.4). The duration of the intervention is noted in minutes, the technical success with "yes/no". Adverse events (description, classification into light, medium, severe and fatal) are documented.

Data documented within the study:

Date of the intervention Start of the intervention

PTBD: Start with skin anaesthesia

EUCD: Start of endoscope insertion End of intervention PTBD: Completion of skin dressing EUCD: Removal of endoscope from patient Dimensions of metal stent

Wrapping of the metal stent Intervention technically successful

PTBD/EUCD: Contrast medium outflow via the metal stent (max. 1min. after injection)

PTBD Localization

PTBD with metal stent implantation

Number of PTBDs before metal stent implantation

PTBD with metal stent release under endoscopic control

EUS-controlled, antegrade drainage (EUS-AD)

EUS-guided transhepatic drainage (EUS-HD)

EUS-guided choledochal drainage (EUS-CD)

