7.2 Efficacy parameters

7.2.1 Technical success of the intervention

Defined by the successful implantation of the metal stent at the respective examination-dependent position

In PTBD:

trans stenotic metal stent implantation, verified by the successful outflow of the contrast medium via the metal stent into the distal intestinal segment (imaging: radiological fluoroscopy; this is not study related)

In EUS-AD:

trans stenotic metal stent implantation, verified by the successful outflow of the contrast medium via the metal stent into the distal intestinal segment (imaging: radiological fluoroscopy; this is not study related)

In EUS-HD:

Metal stent implantation transhepatic, verified by the successful outflow of the contrast medium via the metal stent into the intrahepatic dilated bile ducts (imaging: radiological fluoroscopy; this is not study related)

In EUS-CD:

Metal stent implantation transduodenal into the common bile duct, verified by the successful outflow of the contrast medium via the metal stent into the dilated common bile duct (imaging: radiological fluoroscopy; this is not study related)

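### Technical success, the primary endpoint, is not scored by one stated rule in both arms: only PTBD has a rule for a later stent, and section 7.2.1 describes transluminal EUCD as filling, not drainage

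*Protocol*

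**What the plan says.** The primary objective is confirmatory: "The primary objective of the study is to show that PTBD is not inferior to EUCD in terms of technical success rate". Section 2 defines technical success without naming an arm, as a metal stent in place with "successful drainage of the contrast medium via the metal stent within one minute after injection".

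The same section then adds, for PTBD: "The prompt (1 week) implantation of a metal stent after the application of an external drainage in PTBD is also considered a technical success". The preceding external drainage is counted as a re-intervention, which is a secondary endpoint. For EUCD the section notes a different fallback: "In EUCD, the additional option of transluminal stent placement in the context of EUS-HGS or EUS-CDS remains".

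Section 5.5 defines re-interventions as repeat PTBD or repeat EUCD and accepts that one may be needed to complete the stenting. Section 6.4 starts the visit clock at the successful intervention in both arms. On the data form (section 6.3), technical success is a single contrast-outflow item for PTBD and EUCD with the one-minute limit. The count of earlier sessions exists for one arm only: "Number of PTBDs before metal stent implantation".

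Section 7.2.1 sets out verification by technique:
- PTBD and EUS-AD: "verified by the successful outflow of the contrast medium via the metal stent into the distal intestinal segment".
- EUS-HD: "Metal stent implantation transhepatic, verified by the successful outflow of the contrast medium via the metal stent into the intrahepatic dilated bile ducts".
- EUS-CD: "verified by the successful outflow of the contrast medium via the metal stent into the dilated common bile duct".

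**The concern.** A non-inferiority comparison of two proportions needs a success to mean the same thing in both groups. Two features of the text work against this.

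First, a PTBD patient who leaves the first session without a metal stent can still become a success within a week. For an EUCD patient in the same position the protocol gives no answer. If sites or the analyst score such a patient as a failure, the extra credit goes only to the arm that must be shown non-inferior.

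Second, in EUS-HD and EUS-CD the bile ducts are the structures being drained. Contrast passing through the stent into them shows that the stent is patent and in position, not that bile leaves. If section 7.2.1 were followed literally, EUCD would face a different and possibly easier test than PTBD.

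The endpoint is scored yes or no by unblinded operators, and section 5.3 rests its low-bias argument on the endpoint being objectively measurable. That argument needs a single definition.

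**Working it through.** **1. The plan's own figure.** Inputs from section 9.1: success 0.95 in both groups, margin δ = 0.10, one-sided α = 0.025, power 80%, Farrington-Manning test. The restricted estimates under H0 are 0.8703 (PTBD) and 0.9703 (EUCD).

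- s0 = √(0.8703 × 0.1297 + 0.9703 × 0.0297) = 0.3764
- s1 = √(2 × 0.95 × 0.05) = 0.3082
- n = [(1.960 × 0.3764 + 0.8416 × 0.3082) / 0.10]² = 99.4, so 100 per group
- 100 / 0.95 = 105.3, so 106 per group

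Both stated figures reproduce. The concern does not touch the sample size.

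**2. The scoring rules side by side.**

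| Element | PTBD | EUCD |
| --- | --- | --- |
| Later stent counts as primary success | Yes, within 1 week (section 2) | Not stated |
| Repeat session foreseen | Yes (5.5, 6.4) | Yes (5.5, 6.4) |
| Earlier sessions counted on the form | Yes (6.3) | No item |
| Fallback route within the method | None (section 2) | Transluminal stent (section 2, 5.1) |
| Contrast criterion, sections 2 and 6.3 | Drainage or outflow, one minute | Same |
| Contrast criterion, section 7.2.1 | Into the intestine | EUS-AD: into the intestine. EUS-HD and EUS-CD: into the bile ducts |

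Rows 1 and 3 leave the EUCD score undefined after a failed first session. The last two rows contradict each other for EUS-HD and EUS-CD.

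**3. Possible size of the second-session gap.** The protocol gives neither a first-session PTBD rate nor a rate of stenting in a second session, so both are assumed. EUCD is held at 95% with no second session counted. If first-session PTBD success is s and a fraction r of failures is stented within the week, the counted rate is s + (1 − s) × r. The chance of declaring non-inferiority comes from exact binomial enumeration of the Farrington-Manning test at 106 per arm.

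Take s = 0.85, exactly at the margin, since 0.95 − 0.85 = 0.10:

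| r | Counted PTBD rate | Chance of declaring non-inferiority |
| --- | --- | --- |
| 0 | 0.85 | 2.3% |
| 0.25 | 0.85 + 0.15 × 0.25 = 0.8875 | 14.7% |
| 0.50 | 0.85 + 0.15 × 0.50 = 0.925 | 53.0% |

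**4. Possible size of the verification gap, in the other direction.** Assume EUCD scores 95% as written but only 90% truly drain, with PTBD at 90%. At 106 per arm the chance of declaring non-inferiority is 24.2% on the score as written and 65.3% on true drainage.

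The two effects oppose each other, and the protocol fixes the size of neither.

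**The case against.** Several points on the other side are sound.

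- A reader might infer that EUCD patients are denied a second session. The text does not say so. Sections 5.5 and 6.4 are arm-neutral, and the list of end-of-study reasons in section 6.4 includes an unsuccessful intervention with no new attempt, without naming an arm. What is missing is only the rule and window for counting a repeat EUCD.
- The PTBD clause follows directly on the remark that PTBD has one route and EUCD an extra one. Each arm has its own fallback, and the clause may be a deliberate, prespecified counterweight, although the protocol does not say this. It stands as context, but it does not tell anyone how to score a second EUCD session.
- A reader might infer that EUCD will in practice be scored on filling. That is not shown: the one recorded item in section 6.3 asks for outflow within one minute in both arms. Section 7.2.1 also uses the word outflow and only the destination is odd, so in a translated text a slip is plausible. The one-minute limit being absent there is not a contradiction in itself, because sections 2 and 6.3 state it.
- It is tempting to say that the two biases do not cancel, or that the design favours PTBD. With both sizes unknown, neither can be asserted.
- An example with first-session PTBD at 87%, counted as 93.5%, moves the chance from 6.65% to 66.6% at 106 per arm and looks like inflated error. It is not: 87% against 95% is an 8-point gap, inside the 10-point margin, so the change is a gain in power.

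**Conclusion.** The point holds as an inconsistency in how the primary endpoint is defined and scored. Only PTBD has an explicit rule for counting a later stent, and section 7.2.1 conflicts with sections 2 and 6.3 for two of the three EUCD techniques. It does not establish a bias in a known direction.

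The rise from 2.3% to 14.7% or 53.0% rests on assumed rates (EUCD 95%, first-session PTBD 85%, a quarter or half of failures stented within the week) and on a repeat EUCD not being counted. Those declarations would be false on a first-session reading of the endpoint. On a one-week reading the counted PTBD rates lie inside the margin. That the answer depends on which reading applies is the reason to fix one reading for both arms.

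This should be fixed, and it is a clarification of the definition. The sample size of 106 per group stands.

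**What to change.** - **Section 2:** state one session and time-window rule for the primary endpoint and apply it to both arms. It can be first-session success, or stent in place within 7 days of the first session by the same method. Report the other as a sensitivity analysis.
- **Section 6.3:** record the number of EUCD sessions before stent placement, to match the PTBD item.
- **Section 7.2.1:** reconcile it with sections 2 and 6.3, so that a single drainage criterion with the one-minute limit covers PTBD, EUS-AD, EUS-HD and EUS-CD.

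These are scoring changes; no patient is treated differently. The cost is one form item and some wording. A first-session rule may lower the PTBD rate. It would also leave EUCD its same-session transluminal fallback while PTBD loses credit for its second session, so the protocol should acknowledge that imbalance if it takes that option.
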